## Abstract

Epitranscriptomic modifications in RNA can dramatically alter the way our genetic code is deciphered. Cells utilize these modifications not only to maintain physiological processes, but also to respond to extracellular cues and various stressors. Most often, adenosine residues in RNA are targeted, and result in modifications including methylation and deamination. Such modified residues as *N*-6-methyl-adenosine (m^6^A) and inosine, respectively, have been associated with cardiovascular diseases, and contribute to disease pathologies. The Ischemic Heart Disease Epitranscriptomics and Biomarkers (IHD-EPITRAN) study aims to provide a more comprehensive understanding to their nature and role in cardiovascular pathology. The study hypothesis is that pathological features of IHD are mirrored in the blood epitranscriptome. The IHD-EPITRAN study focuses on m^6^A and A-to-I modifications of RNA. Patients are recruited from four cohorts: (I) patients with IHD and myocardial infarction undergoing urgent revascularization; (II) patients with stable IHD undergoing coronary artery bypass grafting; (III) controls without coronary obstructions undergoing valve replacement due to aortic stenosis and (IV) controls with healthy coronaries verified by computed tomography. The abundance and distribution of m^6^A and A-to-I modifications in blood RNA are charted by quantitative and qualitative methods. Selected other modified nucleosides as well as IHD candidate protein and metabolic biomarkers are measured for reference. The results of the IHD-EPITRAN study can be expected to enable identification of epitranscriptomic IHD biomarker candidates and potential drug targets.

## 1. Introduction

### 1.1. Ischemic Heart Disease

With 8.9 million yearly deaths worldwide, ischemic heart disease (IHD) is the leading cause of mortality [1]. It develops due to atherosclerosis, a process involving lipid and immune-cell buildup into coronary arteries forming calcified deposits, which eventually restrict blood flow to the myocardium [2]. These deposits have a tendency to rupture and occlude blood flow, thus causing myocardial infarctions (MIs). While timely revascularization can alleviate the damage to the myocardium relying on blood supply from the occluded artery, often the dead and injured tissue is replaced by a scar. With the heart devoid of any major regenerative ability, the processes of fibrosis and progressive stiffening often gain dominance and deplete the myocardium’s functional reserve [3]. Initially, the compensatory remodeling mechanisms, including cardiac myocyte hypertrophy, in other areas, can make up for the lost function. However, their extensive activation ultimately leads to structural and functional defects, collectively called maladaptive hypertrophy, compromising the heart’s filling and pumping ability. The resulting heart failure (HF) is a syndrome associated with high morbidity and mortality [4,5]. Disturbingly, IHD can exist asymptomatically without any signs of its existence, only to manifest as a sudden death [6]. Hence, the need for biomarkers capable of exposing IHD is apparent.

The quest for IHD biomarkers has yielded multiple candidates including systemic markers of inflammation and altered metabolism [7,8,9,10,11,12]. However, widespread use of these biomarkers is either limited or preliminary [13,14]. Currently, the diagnostic guidelines focus on the evaluation of symptoms, especially exertional chest pain (*Angina pectoris*) and dyspnea, determination of risk factors, such as age, sex, smoking, dyslipidemias, hypertension, diabetes, and family history of cardiovascular disease and risk factors-based calculators, such as Systematic Coronary Risk Estimation (SCORE) [15,16,17].

The current risk factors and validated risk calculators provide epidemiology-based estimations for the long-term emergence of “hard” IHD-related outcomes (e.g., fatal IHD, MI, stroke), which vary both in time and across cultures [18]. Direct assessment of a disease-associated or disease mechanism-coupled circulating biomarker could promote better-timed, targeted, and more personalized secondary prevention. Moreover, a biomarker capable of mirroring disease progression and regression would be invaluable for the evaluation of therapy efficacy. At best, it could even detect disease in asymptomatic individuals considered at risk of IHD with identical risk factor profiles.

### 1.2. Epitranscriptomics

On a molecular level, the bases of a newly transcribed RNA strand undergo extensive modifications both in the nucleus and cytoplasm. These epitranscriptomic RNA modifications have been identified as regulators of, for example, RNA splicing, silencing, localization, and stability that mediate or regulate a variety of processes involved in tissue homeostasis and disease [19]. In adenosine, the NH2-group at the purine ring’s sixth position may undergo enzymatic deamination to yield inosine (A-to-I) or methylation resulting in formation of N6-methyladenosine (m^6^A). Currently, these A-to-I and m^6^A modifications stand out as the most studied and abundant epitranscriptomic alterations, the extent and effects of which are governed by a variety of proteins (Figure 1) [20,21,22,23,24,25]. However, many other less charted and abundant such modifications have also been identified, including N^1^-methyladenosine (m^1^A), N^5^-methylcytosine (m^5^C), N^7^-methylguanosine (m^7^G), N^6^,2′-*O*-dimethyladenosine (m^6^A_m_), and pseudouridine (Ψ) [20].

Silencing or overexpression of enzymes controlling m^6^A abundance has revealed the role of m^6^A in driving immune reactivity, proliferation, apoptosis, and many intracellular processes including mRNA splicing, translation, and degradation [20,26], as well as miRNA biogenesis [27]. Moreover, reports from diverse fields of research [28,29,30,31], and in an array of cardiovascular pathologies [32,33,34,35,36,37,38,39,40,41,42,43,44,45,46,47,48], provide evidence of m^6^A as a master post-transcriptional regulator.

Since inosines pair with cytosines instead of uracils, the A-to-I modification is capable of diversifying the transcriptome [22]. Like m^6^A, A-to-I editing contributes to RNA stability and innate immunity, but also regulates RNA splicing as well as miRNA biogenesis and function [22,49,50]. Changes in the RNA A-to-I modification landscape have been associated with pathologies including cancer, neurological impairment [49], and cardiovascular disease [25,51,52,53,54,55,56].

### 1.3. Rationale and Goals

The hypothesis of the Ischemic Heart Disease Epitranscriptomics and Biomarkers (IHD-EPITRAN) study states that specific features of IHD are mirrored as epitranscriptomic modifications in the circulating blood RNAs. For example, these changes can manifest as alterations of m^6^A and A-to-I abundance or changes in their decoration patterns or loci within an RNA transcript (Figure 2). Such rationale is suggested by associations between the cellular and molecular processes governed by these modifications and the pathophysiology of IHD. Firstly, formation and dynamics of atherosclerotic plaques could contribute with epitranscriptomic signals into blood since they are the pathophysiological “hotspots” of IHD. They have characteristic features including active inflammatory cell proliferation, altered cellular and paracrine signaling microenvironments, and changes in the luminal presentation of blood cell response-modifying structures [57,58,59,60,61]. Secondly, the myocardium suffering from and responding to varying degrees of ischemia can either directly through e.g., shedding or production of RNA-packed extracellular vesicles (EVs), or priming and altering the patrolling blood cells’ responses contribute to epitranscriptomic cellular or cell-free RNA signature changes in blood. Thirdly, IHD promoting systemic responses, of which for example efflorescence of clonal hematopoiesis (CH) in bone marrow [62,63,64,65,66] and splenic hematopoiesis seeding proinflammatory monocytes [63,67,68] can be expected to alter blood epitranscriptomic signatures. Mechanistically, these postulations are suggested from notions that: (1) some leukocytes (1a) do exit the plaques [69], and (1b) oscillate between circulation and ischemic myocardium [70,71], (2) monocytosis has been independently associated with stable IHD and MI [72,73], (3) m^6^A has been shown to partake in dendritic cell (specialized monocytes) activation [74], (4) METTL3-mediated m^6^A-hypermethylation seems to act as a downstream elicitor of atherogenesis in vascular endothelium in response to disturbed flow and oscillatory shear stress [75], (5) the plaques, juxtaposed platelets, and ischemic myocardium are known to shed EVs to circulation encasing unique miRNAs [59,76,77,78,79,80,81], (6) miRNAs in such EVs have recently been shown to be epitranscriptomically modified [82], (7) epitranscriptomic and epigenetic regulators (7a) are often noted as CH driver mutations [83], and (7b) are pivotal for proliferation of hematopoietic stem cells (HSCs) [31,84,85,86,87,88]. Based on this rationale, the IHD-EPITRAN study aims to identify novel epitranscriptomic biomarkers and drug therapy targets for IHD from blood (Table 1).

## 2. Materials and Methods

### 2.1. Overview

The IHD-EPITRAN study recruits patients with both acute and chronic manifestations of IHD, non-IHD cardiac valve pathology, and healthy controls without IHD. The ethics review board at Helsinki University Hospital (HUS) approved the study protocol (Dnr. HUS/1211/2020). The study is registered at ClinicalTrials.gov (NCT04533282). Written informed consent is acquired from all patients before recruitment. Patient recruitment and follow-up began in November 2020. At the time of submission of this manuscript, the study had enrolled 40 patients. The results are expected to be published between 2022–2026. The study will be conducted following the Declaration of Helsinki on Ethical Principles for Medical Research Involving Human Subjects [89].

### 2.2. Study Groups, Recruitment and Exclusion Criteria

The IHD-EPITRAN study will recruit 50 patients in each of the four study groups to reach its first subgoal of a total of 200 patients. However, the study is expected to continue after the completion of this first phase to increase cohort sizes and study power over time (www.ihd-epitran.com, accessed on 24 May 2021).

The first study cohort (I) consists of patients admitted to the cardiac care unit (CCU) and recruited within 72 h of revascularization via percutaneous coronary intervention (PCI) for MI with ST-elevations (STEMI). The second study cohort (II) consists of patients with chronic coronary syndrome (CCS, typically of category 1: suspected chronic IHD due to anginal symptoms [12]). These are patients with persistent IHD symptoms scheduled to undergo elective coronary artery bypass grafting (CABG) operations. The third study cohort (III) consists of non-IHD patients undergoing aortic valve replacement surgery (AVR) for aortic valve stenosis (AVS). The fourth study cohort (IV) consists of patients diagnosed as negative for IHD with coronary artery computerized tomography angiography (CCTA) imaging. The former two cohorts (I-II) represent patients with IHD while the latter two cohorts (III and IV) represent non-IHD control patients. A chronologic and cross-sectional summary of the study cohorts is provided in Figure 3.

While patients in cohort I will be recruited during the hospitalization period, the cohorts II and III will be recruited during the preoperative visit. Patients in cohort IV will be either (1) preselected based on received referrals by the outpatient-treating physicians to CCTA imaging or (2) contacted after CCTA imaging if it has been negative for IHD within the last 3 months and exclusion criteria are met (Table 2).

All recruited patients will be invited for an echocardiography visit (Section 2.3.4). The study information sheets will be sent well beforehand to ensure familiarization of the study for the candidate participants when possible (cohorts II and IV) and delivered as soon as practical according to the clinical situation in CCU for patients in cohort I. Patients aged 18–80 years and meeting the cohort-specific descriptions are eligible for participation in the study. The exclusion criteria and their rationales are presented in detail in Table 2.

### 2.3. Study Measures

The laboratory methods described below (Section 2.3.5, Section 2.3.6, Section 2.3.7, Section 2.3.8, Section 2.3.9 and Section 2.3.10) for the study sample analytics shape a principal protocol pipeline for the study. However, the authors reserve the rights to alter utilized analysis methodologies to enable both smooth and most appropriate adaptations to the evolving field of epitranscriptomics regarding its methodology as well as pathophysiologial insight.

#### 2.3.1. Baseline Morbidity

To manage the confounding variables, a general baseline morbidity assessment will be performed. The assessment will be carried out using a complementary approach that includes a patient information system search for comorbidities (e.g., hypertension, diabetes, kidney failure, inflammatory conditions, and chronic obstructive pulmonary disease), structured patient interview (Section 2.3.2), and a case report form (CRF) fill-out that includes traditional Framingham cardiovascular risk factors [90], supplemented with body mass index (BMI), personal history of MI, or family history of IHD, determination of SCORE 10-year risk estimates for fatal IHD (for the non-IHD cohorts III-IV) [17], medication list review, coronary imaging (Section 2.3.3), myocardial imaging (Section 2.3.4), and follow- up (Section 2.3.5). Data on patient medication will be curated and analyzed using the InnoLIMS^®^ Medical (Innovatics Ltd., Helsinki, Finland) or equivalent software based on anatomical therapeutic chemical (ATC) classification using the defined daily dose (DDD) values enabling dosage comparisons.

#### 2.3.2. NYHA, CCS and SF-36

*Angina pectoris* and exertional dyspnea, the two central symptoms of IHD, will be graded pre- and postoperatively at the three-month follow-up using the standardized classifications systems from the Canadian Cardiovascular Society (CCS) and New York Heart Association (NYHA) [91]. Further, the 36-Item Short Form Health Survey (SF-36) is used to assess subjective participant morbidity [92].

#### 2.3.3. Coronary Angiography, Computed Tomography Angiogram, SYNTAX Score

An invasive coronary angiography (ICA) will be performed for all participants in study cohorts I–II and for most in AVR control cohort III based on clinical details (mainly for those >50 years of age). ICA will be used to identify the precise site and quality of coronary thrombosis and to focus the PCI revascularization on the cohort I. On the other hand, for the cohort II, ICA will be performed to identify the main culprit segment(s) and to guide the upcoming CABG operation. Critically, based on a clinical risk stratification, either ICA or CCTA will be performed as a screening test to expose either obstructive or non-obstructive IHD, respectively, prior the AVR operation in the AVS control cohort III. All patients in the control cohort IV will undergo CCTA imaging.

While a zero Agatston coronary artery calcium score [12] from CCTA imaging will be required for inclusion to the IHD-EPITRAN study (all in cohort IV, some in III), a synergy between percutaneous coronary intervention (PCI) with Taxus and coronary artery bypass surgery (CABG) (SYNTAX) will be calculated from all ICA results, providing symptom-independent estimates of the complexity of IHD [93]. Moreover, the culprit segment, number, and types of stents or bypasses during PCI or CABG in cohorts I and II, respectively, will be recorded.

#### 2.3.4. Echocardiography, 3-Month Control Visit, and Follow-Up Period

As the development of more sophisticated echocardiographic techniques has revolutionized the field of cardiology and cardiac surgery by offering relevant dynamic insights to both cardiac anatomy and function, IHD-EPITRAN will assess all participants in all cohorts with transthoracic echocardiography (TTE). Critically, the non-IHD control patients in cohort IV will also undergo TTE recording. In this way, valuable functional reference values are obtained.

The TTE recordings will be performed with prespecified acquisition methods by designated cardiologists [94]. The TTE recordings will include both anatomical and functional assessments of atria, valves, and ventricles as well as recording the presence or absence of pericardial effusion, thrombus, and aneurysm. Moreover, the echocardiographic raw data will be exported and stored for further analyses, such as strain and strain rate measurements.

In addition, the 3-month follow-up visit includes a morbidity evaluation with the use of CCS and NYHA and SF-36 questionnaires (Section 2.3.2) alongside routine clinical anamnesis and status. Moreover, the CABG cohort II will undergo ankle-brachial indexing (ABI) to record any asymptomatic peripheral artery disease (PAD).

A six-month prospective follow-up period starting from recruitment will be incorporated. Additionally, a six-month retrospective evaluation will be performed preceding the moment of recruitment. Hospital admission rates with primary cause(s), medication changes, determination of Major Adverse Cardiac and Cerebrovascular Events (MACCE), and all-cause mortality for follow-up make up the parameters assessed both during retrospective evaluation and prospective follow-up.

Hospital admissions regarded as cardiovascular-based will be recorded using the International Statistical Classification of Diseases and Related Health Problems (ICD-10). The IHD-EPITRAN study will use a modified MACCE definition adopted from the ITALIC trial [95] with a composite primary outcome including cardiovascular death, MI, acute revascularization, stroke, transient ischemic attack (TIA), major bleeding (The Bleeding Academic Research Consortium [BARC] classes 3–5), or other hospitalization due to ischemic cardiovascular cause [96].

All-cause mortality with the ICD-10 codes for both underlying and immediate causes of death from the death certificates from the six-month follow-up will be documented with a focus on deaths considered as cardiovascular-related. Cardiovascular medication changes with ATC codes and DDDs will be recorded and analyzed with InnoLIMS^®^ Medical or equivalent software (Section 2.3.1). The medication data yielded will subsequently be used to model either an improved (reduced medication or dosage) or worsened (added medication or increased dosage) disease state.

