**Study cohort IV, patients screened negative for IHD with coronary computed tomography**	
Any prior cardiovascular disease or medication currently or in history	As critical non-IHD controls, the aim is to also recruit patients that represent overall “cardiovascular health”

**Table 3 ijms-22-06630-t003:** Planned outcomes of the IHD-EPITRAN study. Outcome 1 and outcomes 2–5 encase inter- and intra-cohort comparisons, respectively. Morbidity parameters: Section 2.3.2. *A-to-I*, adenosine-to-inosine; *AVR*, aortic valve replacement (III); *AVS*, aortic valve stenosis; *CABG*, coronary artery bypass grafting (II); *CCTA*, coronary computed tomography angiogram (IV); *m^6^A*, N^6^-methyladenosine; *IR*, ischemia-reperfusion; *PCI*, percutaneous coronary intervention; *STEMI*, ST-elevation MI (I).

Primary	Secondary
1. Study sample m6A and A-to-I profiles from the recruitment stage associating with IHD and AVS pathophysiology 1.1. Acute IR controlled for stable ishcemia, pressure overload, and homeostasis (I vs. II-III-IV) 1.2. Stable ishcemia controlled for acute IR, pressure overload, and homeostasis (II vs. I-III-IV) 1.3. Acute IR controlled for homeostasis (I vs. IV) 1.4. Pressure overload controlled for acute IR, stable ishcemia, and hemeostasis (III vs. I-II-IV)	4. Changes in the study sample m^6^A and A-to-I profiles (Recruitment vs. 3-months) associating to 4.1 Therapy effects on Pathophysiology at 3-month follow-up 4.1.1. STEMI-PCI effects (Resolution and relievement acute IR, remodelingl I vs. I) 4.1.2. IHD-CABG effects (Relievement of stable ischemia, remodeling; II vs III) 4.1.3. AVS-AVR effects (Relievement of pressure overload, remodeling; III vs. III) 4.2 All-cause mortality during 3-month follow-up 4.3 Beneficial/adverse/no-response for therapy as measured via echocardiography at 3 months 4.4 Surrogate (non-)metabolite CVD biomarker levels at recruitment, 3 months, changes between
2. Study sample m^6^A and A-to-I profiles from the recruitment stage associating with 3-moth follow-up clinicial parmeters 2.1. Cardiovascular mortality 2.2 Cardiovascular morbidity 2.3. MACCE 2.4 Cardiovascular medication increases or reductions	5. study sample m^6^A and A-to-I profiles from the recruitment stage as in outcomes 4.2.–4.5.
3. Changes in the sample m^6^A and A-to-I profiles (recruitment vs. 3-months) as in outcome 2	6. Study sample quantitative alterations in other RNA modifications as in outcomes 1–5 (2.3.8.)

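### Any added or increased cardiovascular drug is modelled as worsened disease, so treatment changes that belong to the index event or operation would be read as disease course

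*Protocol article*

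**What the plan says.** Section 2.3.4 covers all cardiovascular drugs: "Cardiovascular medication changes with ATC codes and DDDs will be recorded and analyzed". It then gives each change a direction; the data will be "used to model either an improved (reduced medication or dosage) or worsened (added medication or increased dosage) disease state". No drug class, reason or period is exempted.

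The same section sets the windows: "A six-month prospective follow-up period starting from recruitment will be incorporated", and "a six-month retrospective evaluation will be performed preceding the moment of recruitment". Medication changes are assessed in both.

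Section 2.2 fixes when recruitment happens. Cohort I is "recruited within 72 h of revascularization via percutaneous coronary intervention (PCI) for MI with ST-elevations (STEMI"). Cohorts II and III are recruited at the preoperative visit.

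In the primary column of Table 3, outcome 2 relates recruitment profiles to clinical parameters at 3 months and includes "2.4 Cardiovascular medication increases or reductions". Primary outcome 3 applies the same list to changes in the profiles ("recruitment vs. 3-months) as in outcome 2").

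**The concern.** A drug can be added or increased because the disease has progressed, or because the patient has just had an infarction or an operation and treatment is being set up around it. The rule gives both the same code. Likewise, a drug stopped for intolerance or bleeding is coded in the same direction as one stopped because the patient is better.

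Profiles associated with the worsened code could then reflect the care pathway and the regimen at entry instead of the course of ischaemic heart disease. Section 4 expects candidate biomarkers that reflect severity and therapeutic response, so such an association would be easy to misread. Outcome 3 has a further exposure: a drug added between the two samples may itself alter the 3-month profile, and the rule would present that drug effect as a correlate of deterioration.

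**Working it through.** The plan gives no figure for this rule, so there is none to reproduce. The check sets the sections side by side and then illustrates the possible size.

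**1. Does the rule reach a primary outcome?** Outcome 2.4 names increases and reductions without calling either good or bad. Section 2.3.4 is the only place that says what they mean. Reading the two together is an inference, but the article offers no other interpretation.

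**2. What falls inside the window?** The prospective window opens at recruitment.

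| Cohort | Recruitment (Section 2.2) | Changes around the index procedure |
|---|---|---|
| I (STEMI) | within 72 h after PCI | changes after recruitment are inside; those before it fall in the retrospective window |
| II (CABG) | preoperative visit | all changes after surgery are inside |
| III (AVR) | preoperative visit | all changes after surgery are inside |
| IV (CCTA) | no index procedure | not applicable |

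Table 3 reads outcome 2 at 3 months, whereas Section 2.3.4 describes six months. The perioperative period lies inside either window.

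**3. Does anything separate index-related treatment from later escalation?** The article states no reference regimen after the procedure and no reason for change.

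**4. Illustration.** Assumptions, none of them from the documents:
- w is the share of patients who truly worsen.
- s is the share given an added or increased cardiovascular drug as routine care, independent of worsening.
- Every true worsening is labelled, and a single addition or increase is enough for the label.

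From Section 2.2, n = 50 per cohort. Then:
- labelled share = w + (1 − w)s
- positive predictive value (PPV) = w / [w + (1 − w)s]
- specificity = 1 − s

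With w = 0.10:

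| s | Labelled share | Labelled of 50 | PPV |
|---|---|---|---|
| 0.25 | 0.10 + 0.90 × 0.25 = 0.325 | 16.25 | 0.10/0.325 = 0.31 |
| 0.50 | 0.10 + 0.90 × 0.50 = 0.550 | 27.5 | 0.10/0.550 = 0.18 |
| 0.75 | 0.10 + 0.90 × 0.75 = 0.775 | 38.75 | 0.10/0.775 = 0.13 |
| 0.95 | 0.10 + 0.90 × 0.95 = 0.955 | 47.75 | 0.10/0.955 = 0.10 |

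Over the same range of s, PPV runs from 0.17 to 0.05 for w = 0.05, and from 0.50 to 0.21 for w = 0.20. At high s nearly everyone in the cohort carries the label, so it hardly varies and holds little information on disease course.

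**The case against.** - **Outcome 2.4 is neutral.** Table 3 does not use the improved or worsened label, and Section 2.3.4 does not cite Table 3. This stands as a limit: that the label governs 2.4 is inferred. The label is nevertheless the only stated meaning of those changes.
- **The reference regimen may be set elsewhere.** An article can leave such detail to the full protocol or analysis plan. In cohort I, drugs begun before enrolment may already belong to the recruitment regimen. This limits the point in cohort I. It does not help cohorts II and III, where recruitment precedes surgery, and the direction of the coding is stated in the article, not left open.
- **Medication is handled as a confounder.** Section 2.3.1 collects it for that purpose, and Section 2.4 promises adjustment if needed. Adjusting for covariates does not repair an outcome whose categories are mislabelled.
- **The rates are assumed.** No section says which drugs are started or how often, nor that one added drug is enough for the label. This stands, and the numbers above are illustrative only.
- **Cohort IV.** Because Table 2 excludes "Any prior cardiovascular disease or medication currently or in history", a reader might infer that its one-directional scale biases comparisons with the other cohorts. The Table 3 caption makes outcomes 2-5 intra-cohort, and Section 2.3.5 samples cohort IV only once, so it cannot enter outcome 3. That inference is not supported.

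**Conclusion.** The concern holds as a badly fixed definition: a signed rule without regard to reason or timing, applied over a window that contains the index operation in cohorts II and III and the period after recruitment in cohort I. That treatment changes around these events is a clinical premise; that the rule would code any such change as disease course follows from its wording.

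The size is unknown. The PPV range of about 0.31 to 0.10 depends wholly on the assumed 10% true worsening and 25-95% routine additions.

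A reader might go further and infer that the sign of the outcome is reversed for many cohort I patients. The documents do not support this. They give no starting rates, and a low PPV shows misclassification, not reversal. Outcome 1 and the sample-size calculation in Section 2.4 are unaffected.

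**What to change.** 1. Delete the improved/worsened label from Section 2.3.4.
2. Analyse outcome 2.4 as neutral increases or reductions by ATC class and DDD, within cohort, against a stated reference regimen after the index procedure (at recruitment for cohort IV).
3. Record the reason for each change. Treat a change as disease-related only where that reason is new or worse symptoms or an ischaemic event.
4. Otherwise use medication as a covariate, particularly for outcome 3.

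Outcome 2.4 need not leave the primary outcomes; moving it would be a preference, not a correction. This changes the analysis only and proposes no treatment rule.

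Cost: ATC and DDD data are already planned, so one reason-for-change field is added. For the 40 patients enrolled at submission it would be abstracted from records. For the other 200 − 40 = 160 of the first-phase target it could be collected prospectively if adopted at that point. Fewer patients will count as changed, which reduces the information available for 2.4.
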